**Methods/Design:**

Data will be collected at six New South Wales (NSW) primary schools, on physical activity levels, on-task time during classes, and social support for physical activity during a 12 month Cluster Controlled Trial (CT). Three quantitative data collection tools will be used to capture student’s physical activity levels during lunch and recess breaks (the SOPARC tool), student’s on-task behaviour during classes following recess and lunch breaks (the BOSS tool) and where students receive the most encouragement to be physically active from (the Physical Activity Social Support Scale survey). Baseline data will be analysed against follow-up data, collected after an intervention that is rolled out in all schools as part of a stepped wedge CT design.

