## Methods/Design

### Study Design

The Healthy Active Peaceful Playgrounds for Youth (HAPPY) study is a 12 month, primary school-based intervention and will be evaluated using a cluster controlled trial with a stepped wedge design. Ethics approval has been obtained from an Australian University Human Ethics Committee (HREA5201500676) as well as from the New South Wales Department of Education and Communities (SERAP2015423). The HAPPY Study is registered with the Australian and New Zealand Clinical Trials Registry (ACTRN12616000575437). Principals, teachers and parents will provide written informed consent.

Following the recruitment process, data will be collected on students’ physical activity levels during lunch and recess, students’ on-task behaviour during class following lunch, and from whom the students receive social support from to be physically active. The intervention will be rolled out in a stepped wedge design. This means that all schools will start as ‘control’ schools and that the intervention will staggered across the 12-month period of the study (three steps in total) with data will being regularly collected across the period (Fig. 1). The stepped wedge design allows for an analysis of the interventions effectiveness and efficacy. As well as having the added benefit of ensuring all schools receive the intervention [16] (i.e., playground markings and teacher training). This benefit is often absent in classic Randomised Control Trials, where control groups may receive no immediate benefit from participating in research studies. This was the main rationale behind adopting this stepped wedge design.

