### Statistical methods

Using the Statistical Package for Social Sciences (SPSS, v21), descriptive statistics and measures of central tendency will be used to describe the effect of the intervention from baseline to follow-up data in each step of the study.

Regression analysis will be completed for this study, to determine genuine relationships between the intervention, and the outcomes for physical activity levels, students’ on-task behaviour time, and frequency of social support for physical activity. Mixed-model ANCOVAs in SPSS will be computed, and each mixed model will be fitted to the data using the restricted maximum likelihood method. Percentage of occurrence (i.e. frequency) data will be analysed using ×2. For each mixed model, sex will be included as fixed effects, with the school included as a random effect to account for the effects of stepping by school. This is a standard statistical procedure for analysis of clustered datasets [27].

Intra-cluster comparisons will be completed between control and intervention periods, and for analyses involving school level characteristics of physical activity, the unit of analysis will be one scan of one area.

If schools decide to stop participating in the study, data pertaining to that school will not be included in the final analyses. Likewise, if a student selected for the behavioural observation component of the study decides to stop participating in the study their data will not be used in the final analyses. For all other components of the study (i.e., physical activity observation and Social Support), intention to treat principles will be followed and all possible data collected will be analysed.

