A key strength of this study is the stepped wedge cluster controlled trial design. The design of the study means that time can be used as a variable to measure the effect of the intervention overtime. The design of the study also enables the research team to run the intervention in all schools over the 12-month study period. While this is thought to be ethical [30], it is also likely to decrease attrition.

If this study is successful in increasing students’ physical activity levels and modifying students’ behaviour, future research could include examining which aspects of the intervention produce which effects.

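### The school random effect is given the job of handling the stepping, but it cannot remove a time trend shared by all schools, and no stated effect model includes school term.

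*Protocol article*

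**What the plan says.** The Statistical methods section of the protocol article specifies mixed-model ANCOVAs fitted by restricted maximum likelihood. For each of them, "sex will be included as fixed effects, with the school included as a random effect to account for the effects of stepping by school". The section calls this standard for clustered data. It then states that "Intra-cluster comparisons will be completed between control and intervention periods". Descriptive statistics are to "describe the effect of the intervention from baseline to follow-up data in each step of the study", and the abstract says "Baseline data will be analysed against follow-up data, collected after an intervention that is rolled out in all schools".

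Under Study Design, "all schools will start as" control schools, and "the intervention will staggered across the 12-month period of the study (three steps in total"). The recruitment section puts all six schools' baseline in the same school term and randomises them to step groups afterwards.

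Two other places touch on time. The section on physical activity during recess and lunch lists, for the SOPARC data, an analysis within each school, one between all schools in the same collection period, and one on all data. The Discussion says "time can be used as a variable to measure the effect of the intervention overtime".

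**The concern.** Two separate problems are run together in the sentence on the random effect. Clustering means that observations from one school resemble each other, and a school random effect deals with that. Stepping means that schools change condition at different calendar times, always from control to intervention, so treated observations are later on average. Adjusting for that needs a term for time. A school intercept has the same value in every term and cannot represent a change common to all schools.

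The within-school contrast does not help. Comparing each school's later treated terms with its own earlier control terms carries the shared trend in full.

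Drift over a school year is plausible from the protocol's own content. Temperature, rain and UV are recorded at every scan but are not named as covariates, and the same five pupils per school are observed in class at each collection point while they grow older. What protects a stepped wedge against drift is the comparison, in the same term, of schools that have crossed over with schools that have not. The stated effect model does not secure that comparison.

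**Working it through.** **Inputs from the protocol article.** Six schools; three steps over 12 months; a common baseline term; 12 scans per school per term; 288 scans in total; 1,661 students to be observed.

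**The plan's own figure.** 12 scans × 6 schools × 4 terms = 288. The total reproduces and implies four terms, which fits one baseline term plus three steps.

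**Assumptions (not in the document).** Two schools per step, since the design figure is not shown; total SD 1; ICC 0.05; linear drift D per term common to all schools; no true effect; two-sided 5% test; known variances.

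**Step 1: timing of the two conditions.** Mean intervention term minus mean control term, by crossover:
- from term 2: 3.0 − 1.0 = 2.0
- from term 3: 3.5 − 1.5 = 2.0
- from term 4: 4.0 − 2.0 = 2.0

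Control schools by term are 6, 4, 2, 0 and intervention schools 0, 2, 4, 6. Ignoring school, the mean control term is (6×1 + 4×2 + 2×3)/12 = 1.67 and the mean intervention term is (2×2 + 4×3 + 6×4)/12 = 3.33, a gap of 1.67. The drift-induced estimate therefore lies between 1.67D (no weight on the within-school contrast) and 2.0D (purely within school). A stronger school effect moves it towards 2.0D.

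**Step 2: model with intervention and school random intercept, no term effect.** The covariance of a school's four term means is V = [(1 − ICC)/n]·I + ICC·J, with n observations per school-term. Generalised least squares gives bias b and standard error SE. The rejection probability is 1 − Φ(1.96 − b/SE) + Φ(−1.96 − b/SE).

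One row in full, n = 12 and D = 0.05: b = 1.893 × 0.05 = 0.095; SE = 0.122; b/SE = 0.77; rejection = 12%.

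| Observations per school-term | D (SD per term) | b (SD) | SE | False positives |
|---|---|---|---|---|
| 12 (scans) | 0.05 | 0.095 | 0.122 | 12% |
| 12 | 0.10 | 0.189 | 0.122 | 34% |
| 69 (1,661/24) | 0.05 | 0.099 | 0.052 | 47% |
| 69 | 0.10 | 0.197 | 0.052 | 97% |

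The 12-scan rows match the unit of one scan of one area that the protocol sets for school-level activity analyses. The 69 rows spread the stated 1,661 evenly over 24 school-terms.

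**Step 3: other shapes of drift (n = 12).** A change confined to the first or the last term puts 57% of its size into the estimate. A pattern equal in terms 1 and 4 and equal in terms 2 and 3 gives exactly zero bias.

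**Step 4: add term as a four-level fixed effect.** Bias from any drift common to all schools becomes 0, and the rejection rate under no effect is 5.0%. SE rises from 0.122 to 0.201 at n = 12 (variance ratio 2.71) and from 0.052 to 0.089 at n = 69. Over ICC 0 to 0.30 the variance ratio runs from 2.25 to 3.0.

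**Step 5: limit of that 5%.** It also assumes that a school's level does not vary from term to term beyond the shared trend. With n = 69, if the between-term correlation within a school is 0.8 of the within-term correlation and the model ignores this, the rejection rate is 13%; at 0.5 it is 24%. These ratios are assumed.

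**The case against.** The strongest reply is that the sentence is not a complete model. It names no intervention indicator either, although the same section says the regression is about the intervention, and an ANCOVA without a named covariate is plainly abbreviated. In a condensed article, a term effect could simply be left to the full analysis plan. This stands as a limit: a reader might infer that the final analysis will certainly have no period term, and the document does not support that. It does not rescue the stated reason. The article does not stay silent on stepping; it assigns stepping to the school effect, which is wrong whatever else the model contains.

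Second, the SOPARC section plans a comparison between schools in the same collection period, and the Discussion says time can be used. A reader might conclude that the randomised order goes unused altogether; for physical activity that is too strong. But the same-period analysis is one of three listed without being tied to the effect model, it covers SOPARC only, and the Discussion remark names no model term. On-task behaviour and social support have no equivalent.

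Third, a reader might infer that any drift biases all three outcomes. It does not: a seasonal pattern symmetric about mid-study cancels in the assumed layout. That is a reason for conditional wording, not for relying on the cancellation.

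Fourth, baseline-to-follow-up is already assigned to descriptive statistics in the Statistical methods section. That is correct. The looser wording is in the abstract and in the within-school comparison.

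**Conclusion.** The point holds in conditional form. The article gives the school random effect a task it cannot perform, names sex as the only fixed effect, and plans within-school contrasts in which intervention always comes later. Drift that is shared by the schools and not symmetric about mid-study would be counted as intervention effect. The remarks on same-period comparison and on time as a variable do not put period into the effect model and need to be reconciled with it.

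The multiplier of about 1.9 to 2.0 times the drift per term follows from the inferred layout and ICC 0.05. The false-positive rates depend heavily on the amount of data per school-term and on an assumed linear drift, so they illustrate and do not forecast. The high rates of 47% and 97% should not be read as the expected error: they need about 69 observations per school-term, whereas the scan as unit gives 12% and 34%. No rate was computed for on-task behaviour (30 pupils) or the social support survey. For those, only the direction of the argument carries over.

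**What to change.** In the Statistical methods section, for every outcome model:
- include school term as a categorical fixed effect and a time-varying intervention indicator that follows each school's randomised step;
- base the conclusion on the intervention coefficient from that model;
- label the within-school control-versus-intervention comparisons, and the abstract's baseline-versus-follow-up contrast, as descriptive;
- state that the school random effect accounts for clustering and that the term effects account for calendar time;
- align the SOPARC analysis paragraph and the Discussion remark on time with this model.

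The text change is small and no new data are needed. The cost is precision: in the illustration SE rises from about 0.12 to 0.20 SD at 12 scans per school-term and from 0.05 to 0.09 at 69, so the sample-size statement should be rechecked against the model with term effects. With only six schools, a school-by-term random effect or a small-sample correction may also be needed to keep type I error near its nominal level.

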### Recruitment and study participation

The HAPPY Study will be conducted in six New South Wales Department of Education and Communities (NSWDEC) schools, in the Metropolitan Sydney Region (approx. 33.51°S, 151.12°E). All eligible schools will be sent an invitation to participate by the NSWDEC Schools Sport Unit. Schools that express an interest in participating will be contacted by the research team, and will be provided with more information about the study and intervention.

To participate, schools will be required to provide school level consent for the physical activity observational data collection from the principal, and all students participating in the behavioural, and the social support data collection will be required to provide parent/guardian consent. Teachers will not need to provide consent to participate in the intervention, as no information identifying them will be recorded or reported on.

All six schools will be participate in baseline data collection during the same school term and randomisation into stepped intervention groups will take place after the baseline data.

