### Physical activity during recess and lunch

Observational data will be collected on student’s physical activity levels during lunch and recess breaks, and their utilisation of playground spaces for physical activity recorded using the System for Observing Play and Recreation in Communities (SOPARC) tool (CIAFEL, Portugal: http://activelivingresearch.org/soparc-system-observing-play-and-recreation-communities). This tool will collect student’s sex, their level of physical activity and environmental factors (i.e. time of day, temperature, recess/lunch break, presence of supervision).

SOPARC is a sampling technique in which systematic and periodic scans of individuals and environmental factors within predetermined target areas are made. Each school will have two predetermined target areas, identified by the Principal of participating schools as areas that students use frequently during recess and lunch. Following SOPARC protocols developed in a previous study [20, 21], trained researchers will complete two scans of each areas at both recess and lunch, three times during each term the study is running. The researchers are blind to the conditions of the intervention. Each school in the study will therefore be scanned 12 times each term, for a total of 288 scans across all schools during the study.

A scan involves panning from left to right, and coding each student in the area by sex (male or female), intensity of activity (Sedentary, Walking or Vigorous), and whether they are a Child, Teen, Adult or Senior. Additional data recorded for each scan will include; 1. Weather variables including temperature, rain and UV levels; 2. Time of day the observations were collected, and whether this was a lunch or recess period; 3. What type of activity the students are engaged in (i.e. handball, football, dancing, clapping games) and; 4. Teacher supervision and direction of physical activity. The SOPARC tool has been used by this research team to collect physical activity and sun-safe behaviours in primary schools, and was found to be efficient to use and had high degree of reliably, with an Intraclass Corelation Coefficient (ICC) of .912 [21].

Analysis of data collected with SOPARC will be done at an individual school level, between all schools during the same collection period and then completed on all data collected during the study.

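### A school-only random effect sets visit-day and school-by-term variation to zero, so the intervention effect's standard error is too small wherever that variation is material

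*Protocol article*

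**What the plan says.** Under Statistical methods, the protocol article specifies mixed models fitted by restricted maximum likelihood. For each one, sex is a fixed effect, "with the school included as a random effect to account for the effects of stepping by school". No other random effect is named, and the article calls this standard for clustered data. The same section adds that, for analyses of school-level characteristics of physical activity, "the unit of analysis will be one scan of one area".

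The design is described elsewhere in the article:
- Recruitment and study participation: "The HAPPY Study will be conducted in six New South Wales Department of Education and Communities (NSWDEC) schools".
- Study Design: "the intervention will staggered across the 12-month period of the study (three steps in total".
- Physical activity during recess and lunch: "Each school will have two predetermined target areas", and "trained researchers will complete two scans of each areas at both recess and lunch, three times during each term the study is running". The stated yield is 12 scans per school per term, "for a total of 288 scans across all schools during the study".

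The article gives no significance level and no variance component for area, visit day or school-by-term.

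**The concern.** Scans made at one school on one day share the same children, weather, supervision and events. Scans made in one school-term also share whatever is particular to that school in that term. The intervention is switched on for a whole school at a step, so a chance fluctuation at school-term level coincides with the contrast being estimated. A school intercept removes stable differences between schools. It does nothing for variation between terms or days within a school, which the model counts as independent scan noise to be averaged over all scans.

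At stake is the inference on playground physical activity. The confidence interval may be too narrow, and a few unusual school-terms could be reported as an intervention effect. A degrees-of-freedom correction applied to the stated model would not cure this, because the missing component is not in the model at all.

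**Working it through.** **Reproducing the plan's count.** 6 schools × 12 scans per term × 4 terms = 288, the stated total. The trial therefore covers four terms, which fits one baseline term plus three steps, and there are 6 × 4 = 24 school-term cells. Taken literally, the schedule gives 2 scans × 2 areas × 2 breaks × 3 visits = 24 scans per school-term, or 24 × 6 × 4 = 576. Both counts are carried below; 12 is the stated one.

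**Assumptions, because the article gives no figure.** Two-sided 5% level; two schools per step; the same two areas observed throughout. As shares of within-school variance, let *a* be area, *v* visit day, *s* school-by-term, and *e* = 1 − *a* − *v* − *s* the remaining scan noise. Let *n* be the scans per school-term.

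**Hand calculation.**
- True variance of a school-term mean, after school and term effects: *s* + *v*/3 + *e*/*n*. Area drops out because each cell contains both areas equally.
- Variance the school-only model implies: (*a*/2 + *v* + *s* + *e*)/*n*. The *a*/2 arises because two areas around their school mean leave half the area variance within the school.
- Ratio of reported to true standard error: *R* = √(implied/true).
- Approximate type I error: 2[1 − Φ(1.96 *R*)].

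Example, *n* = 12, *v* = 0.10, *s* = 0.05, *a* = 0: true = 0.05 + 0.10/3 + 0.85/12 = 0.1542; implied = 1/12 = 0.0833; *R* = √(0.0833/0.1542) = 0.735; type I error = 15.0%.

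| *a* | *v* | *s* | *n* | implied | true | *R* | type I |
|---|---|---|---|---|---|---|---|
| 0 | 0 | 0 | 12 | 0.0833 | 0.0833 | 1.000 | 5.0% |
| 0 | 0.05 | 0.01 | 12 | 0.0833 | 0.1050 | 0.891 | 8.1% |
| 0 | 0.10 | 0.02 | 12 | 0.0833 | 0.1267 | 0.811 | 11.2% |
| 0 | 0.10 | 0.05 | 12 | 0.0833 | 0.1542 | 0.735 | 15.0% |
| 0 | 0.20 | 0.05 | 12 | 0.0833 | 0.1792 | 0.682 | 18.1% |
| 0.30 | 0.05 | 0 | 12 | 0.0708 | 0.0708 | 1.000 | 5.0% |
| 0 | 0.05 | 0.01 | 24 | 0.0417 | 0.0658 | 0.796 | 11.9% |
| 0 | 0.10 | 0.02 | 24 | 0.0417 | 0.0900 | 0.680 | 18.2% |
| 0 | 0.10 | 0.05 | 24 | 0.0417 | 0.1188 | 0.592 | 24.6% |
| 0 | 0.20 | 0.05 | 24 | 0.0417 | 0.1479 | 0.531 | 29.8% |

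**Simulation.** Null trials of this layout were analysed with a school intercept only, at scan-level degrees of freedom, with term effects added (the article does not list term).
- *v* 5–10% with *s* 1–2%: about 8–12% at 12 scans, 12–18% at 24.
- *s* 5% with *v* 10–20%: about 15–18% at 12 scans, 24–32% at 24.
- *s* alone at 2, 5 and 10%, 12 scans: 8.3, 12.7 and 18.7%, with reported standard errors 0.88, 0.79 and 0.67 of the true ones.
- Area alone at 10–30%: 2.7–5.2% across both scan counts, with and without term.
- *a* 30%, *v* 2%, *s* 1%: 5.4% at 12 scans, 8.4% at 24.
- Only a school intercept in the data, 12 scans: 6.5% with term in the model, 5.0% without. Six schools alone add little.
- Leaving term out, with no time trend in the data, changed the results only slightly.

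**Alternative.** The 24 school-term means, with school, term and intervention effects, leave 24 − 6 − 3 − 1 = 14 residual degrees of freedom. Type I error was 3.9–5.7% in every scenario tried.

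**The case against.** The strongest reply is that nobody knows the variance shares. If visit-day and school-by-term variation is negligible, the stated model is sound. With large area variance and tiny other shares it stays close to 5% at 12 scans. Weather, time and supervision are recorded at each scan, and as covariates they could absorb some visit-day variation. This is also a condensed article, and a full covariance structure often sits in a later document. Finally, the unit-of-analysis sentence covers only school-level characteristics, not every model.

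Much of this stands, and it makes the size conditional. It does not remove the point. The random-effect sentence applies to each mixed model and states a specific structure, so this is not merely missing detail. The recorded covariates are not among the listed model terms. Nothing in the article supports treating the two variances as zero.

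Three stronger readings are tempting and not supported:
- **Shared area as a cause of false positives.** Both areas are seen in control and intervention periods, so leaving out a stable area effect makes the test neutral to conservative.
- **Only 24 independent units.** Without school-by-term variance, the independent level is the visit: 24 × 3 = 72. Nor are the 24 cells independent of one another, since they share schools and terms.
- **Error rates near 30% under the stated schedule.** Those need 24 scans per school-term, against the stated 12.

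**Conclusion.** The point holds in conditional form. The stated model is valid only if visit-day and school-by-term variation is negligible, which the article neither claims nor supports. Where either is material, the standard error of the intervention effect is too small. At the stated 12 scans per school-term, type I error is about 8–12% for modest assumed shares and 15–18% for larger ones. On the literal schedule of 24 scans, the same shares give about 12–18% and 24–32%.

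A reader might infer that false positives must exceed 5%. The documents do not support that: the net result depends on shares they do not give, and area variance pushes the other way. Confidence is high on the mechanism and moderate on the size. The figures rest on the assumed shares, four terms, two schools per step, a two-sided 5% level and term effects in the model.

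**What to change.** Replace the school-only structure for the scan data. Alongside school, add random effects for school-by-term and for visit day, and use small-sample degrees of freedom such as Satterthwaite. Area within school may be added for precision; it is not needed to protect the error rate.

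As a simple robust alternative or check, analyse the 24 school-term means with school and term effects on 14 residual degrees of freedom. This is not identical to the multi-level model, which was not itself simulated.

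A permutation test over the allocation of schools to steps is an optional supplement. With two schools per step there are 6!/(2! 2! 2!) = 90 allocations; that count depends on the assumed split.

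The cost is revised analysis wording, a little programming and a wider confidence interval. No new data are needed.

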### Sample size calculation

The stepped wedge design used for this study is a variant of a Cluster Controlled Trial where all clusters receive the intervention in a randomised order. Taking into account the possibility of intra-cluster correlation [16], an effect sample size for physical activity observations was calculated using ESS = (m × k/DE) assuming that schools will have an average of 500 students enrolled, the design effect was 0.05. It was calculated that 1661 students would need to be observed to provide adequate power to detect a difference between clusters receiving the intervention.

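### Excluding every school that stops is not compatible with the intention-to-treat claim for physical activity and social support; the student rule for observed behaviour is a separate completers-only choice

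*Protocol article*

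**What the plan says.** All the rules on stopping are in the last paragraph of Statistical methods in the protocol article.

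- **Schools:** "If schools decide to stop participating in the study, data pertaining to that school will not be included in the final analyses". The sentence is not limited to one outcome or to data after withdrawal.
- **Students in the behaviour component:** if a selected student stops, "their data will not be used in the final analyses".
- **Everything else:** the next sentence begins "For all other components of the study (i.e., physical activity observation and Social Support" and, for those two components, promises that "intention to treat principles will be followed and all possible data collected will be analysed".

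The unit of randomisation is the school. Under Sample size calculation, "all clusters receive the intervention in a randomised order". Under Recruitment and study participation, "randomisation into stepped intervention groups will take place after the baseline data". There are six schools. The same Statistical methods section plans mixed models fitted by restricted maximum likelihood, with school as a random effect.

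**The concern.** An intention-to-treat analysis keeps the randomised units in the analysis as they were allocated. The school rule removes a randomised unit because of something that happens after allocation, and removes valid control-period and intervention-period data collected before the school stopped. If stopping is related to the programme or to when a school receives it, the remaining schools are a selected set and the estimate may be biased.

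Precision is also at stake, because each of six clusters carries much of the information. The planned mixed model can use a school with an incomplete series of terms, so the method of analysis does not require the exclusion.

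The student rule raises a smaller version of the same issue. Measures already taken on a student in a randomised school are discarded when that student stops, and students who stop may differ from those who stay.

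**Working it through.** **1. The three sentences side by side, when a school stops**

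| Outcome | School sentence | Student sentence | Intention-to-treat sentence |
|---|---|---|---|
| Physical activity (SOPARC) | leave the school out | does not apply | analyse all possible data |
| Social support survey | leave the school out | does not apply | analyse all possible data |
| Classroom behaviour (BOSS) | leave the school out | leave out a student who stops | does not apply (carved out) |

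The first two rows conflict; the third does not. For physical activity the school is the only unit that can withdraw: scans code children by sex, intensity and age group, and consent comes from the principal. Once schools that stop are removed, no withdrawal is left in that component for the intention-to-treat sentence to cover.

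**2. Share of the data in one school**

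- Clusters: 1/6 = 16.7%.
- Scans: the article states 12 per school per term and 288 in total; 12 × 6 × 4 = 288, so one school has 288/6 = 48.
- Students observed for behaviour: 5 of 30.

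**3. Effect on precision**

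The article gives no figure for this, so there is none to reproduce. The calculation needs assumptions, partly because Fig. 1 is not shown.

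- *Layout:* six schools, three steps and four terms. Six schools and three steps are stated; four terms follows from the scan total. Two schools per step is assumed, with all schools as controls in term 1.
- *ICC 0.05:* assumed. The article gives 0.05 but calls it a design effect.
- *Observations per school-term:* 1661/(6 × 4) = 69. This takes the article's required number as given; that number could not be reproduced from its stated formula and inputs.
- *Cluster autocorrelation:* 0.8 to 1.0, assumed, and equal for every pair of terms.
- *Model:* fixed term effects plus an intervention effect. Term effects are an assumption, because the stated model lists only sex (fixed) and school (random).

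For school *i* with observed terms, let *X* hold the term indicators and the intervention indicator. The covariance *V* of its term means has ICC + (1 − ICC)/69 on the diagonal and ICC × autocorrelation off it. The variance of the effect is the corresponding diagonal element of (Σ X′V⁻¹X)⁻¹. The ratios below are relative to complete data when one school stops.

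| Step of the school | School excluded | Terms 1–3 kept | Terms 1–2 kept | Term 1 only kept |
|---|---|---|---|---|
| 1 | 1.29 | 1.04–1.05 | 1.05 | 1.29 |
| 2 | 1.17–1.18 | 1.00 | 1.11–1.12 | 1.17–1.18 |
| 3 | 1.29 | 1.04–1.05 | 1.22 | 1.29 |

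Exclusion therefore raises the variance by 17–29%, which is √1.17 = 1.08 to √1.29 = 1.14 on the standard-error scale. Keeping the data recovers most of this if the school stops after term 3. If it stops after term 2, the recovery depends on the step. If it stops after term 1, nothing is recovered: a single term in which every school is a control does not help to estimate the effect in this model.

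A wider set of assumptions (ICC 0.01–0.10, 12–500 observations per school-term, autocorrelation 1) gives a similar picture on the standard-error scale: a rise of about 6–15% if the school is excluded, 0–3% if only the last term is missing, and 2–11% if the last two are missing.

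**The case against.** The best defence is that the sentences can be read in order: a school that stops is out of everything, a student who stops is out of the behaviour analysis, and in the remaining schools all collected scan and survey data are used. This reading is workable, so it would be too strong to say that the paragraph cannot be carried out. It does not rescue the intention-to-treat claim, because a randomised school is still dropped for a later event.

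Three stronger readings are tempting, and the document does not support them.

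- *That the student rule also contradicts intention to treat.* It does not. The intention-to-treat sentence covers only the other components, so behaviour is an announced exception. The observed students are identified by their schools and are not themselves randomised.
- *That data are deleted.* The text says only that they are not included or not used in the final analyses.
- *That exclusion favours the intervention.* Nothing in the article shows that schools that stop would be those where the programme fails, or that students who stop would be the most off-task. Schools may stop for unrelated reasons, even while still controls.

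It is also fair to say that the rule matters only if someone stops. The article gives no expected attrition and, in its Discussion, expects the design to reduce it. Non-use of a withdrawn child's data may also reflect consent terms that are not shown. These points lower the priority and call for a consent exception in the fix. They do not justify leaving a randomised school out by default.

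**Conclusion.** The point holds at school level. If a school stops, the stated exclusion gives a completers-only analysis at the level of randomisation, and the intention-to-treat claim for physical activity and social support is not met. Bias is possible, of unknown direction and size. The loss of precision from exclusion is about 17–29% in variance. How much of that is avoidable depends on timing: most of it after term 3, a variable part after term 2, none after term 1. These percentages rest on the assumed layout, ICC, cluster size and term effects; the shares of one school (1/6 of clusters, 48 of 288 scans, 5 of 30 students) follow from the article's stated totals.

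The behaviour rule is a separate, weaker point: a declared completers-only choice that discards usable repeated measures from a 30-student sample. Both rules should be fixed before the data are analysed. Because the effect depends on a school or student actually stopping, this is a should-fix and not a must-fix.

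**What to change.** Replace both exclusion sentences with one rule, for example: *All data collected up to withdrawal are retained and analysed by the step to which the school was randomised, for all three outcomes, unless consent to use collected data is withdrawn.* Report the completers-only analysis, for schools and for observed students, as a sensitivity analysis.

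The cost is small. It is a change of analysis wording with no new data collection, and the planned mixed model can handle the incomplete series. The consent form may need a line on the use of data already collected, which should be checked before the rule is adopted.
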